# VI. Observation items and testing time point

| Observations | Time point of testing |
| --- | --- |
| Precision of catheter tip position | Day of surgery |
| Length of surgery | Day of surgery |
| Confidence of the catheterization nurse | Day of surgery |
| Postoperative Infection | Postoperative day 3 |
| Incidence of intraoperative adverse events | Day of surgery |

# VII. Efficacy Assessment Criteria

1. Effectiveness index
2. Main observation indexes
3. Precision of catheter tip position (Time: the day of surgery)
   1. DEFINITION: The American Society of Infusion Nursing considers the optimal location for the tip of the central venous catheter to be the superior vena cava junction (CAJ), i.e., the junction of the superior vena cava with the right atrium or the lower third of the superior vena cava (SVC) in its vicinity. In this study, the catheter tip was considered to be accurately positioned when it was shown on postoperative CT to be in the CAJ or the lower third of the SVC.
   2. Calculation: $导管尖端位置精准度=\frac{导管尖端位置精准病例数}{总样本量}\times100\%$
   3. Evaluation method: chest CT was taken immediately after the subject's operation and interpreted by a physician with relevant experience.
4. Secondary evaluation indicators
5. Surgical time (time: the day of surgery)
   1. Definition: The length of time from the beginning of the catheterization operation by the catheterization nurse to the fixation of the catheter.
   2. Evaluation method: The length of time was recorded by the recorder.
6. Economy (time: within 3 days after the intervention)
   1. The time spent by the subjects on catheterization, the number of cases and time spent on secondary postoperative adjustment of the catheter tip position, and the medical costs were counted.
   2. Statistical analysis of economic-benefit indicators.
7. Confidence of the catheterization operator
   1. Definition: Confidence of the catheter placement operator in positioning the catheter tip to the optimal position with ultrasound assistance.
   2. Evaluation method: A qualitative interview was conducted in the form of a postoperative interview with the catheterization operator, with the following outline: 1. How long has your catheterization/harboring experience been? 2. Have you had difficulty in positioning the catheter tip in the past? 3. Do you feel more confident in your operating technique when ultrasound-assisted catheterization is performed? 4. Do you feel more confident in positioning the catheter in the optimal position when ultrasound-assisted catheterization is performed? 5. think that the use of ultrasound interferes with your catheterization?
8. Safety Indicators
9. Incidence of surgical site infection (Time: 3 days postoperatively)
   1. Definition: in this study, it refers to infections occurring at the PICC placement site or at the PORT capsular bag, with clinical manifestations including localized redness, swelling, warmth, pain and tenderness.
   2. Calculation:$术后感染发生率=\frac{发生术后感染的病例数}{总样本量}$× 100%

[figure not shown]

- 1. Evaluation method: the clinician judged whether the infection occurred according to the subject's symptoms and the Chinese Guidelines for the Prevention of Surgical Site Infections.

1. Incidence of intraoperative adverse events (Time: the day of surgery)
   1. Definition: This study refers to adverse events that occurred during tube placement.
   2. Calculation: Intraoperative adverse event incidence rate =$\frac{发生不良事件的病例数}{总样本量}$

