# V. Research Methods and Technical Route

1. Subject enrollment

Patients were enrolled in the order of catheterization.

1. Intervention/Study drug name and specification

In this study, trans-thoracic wall cardiac ultrasound was used to locate the position of the catheter tip, all intraoperative ultrasound exploration steps were done by one doctor, tube placement steps were done by one nurse, and postoperative CT examination was performed in the imaging department of our hospital.

(1) Instruments

Ultrasonic instrument

(2) Methods

Ultrasound localization catheter tip operation procedure:

a. Patient position preparation: the patient takes a flat lying position, and the catheterization arm is placed at 90° to the torso;

b. Disinfecting and spreading the towel: measure the arm circumference, disinfect the catheter placement site, and spread the towel;

c. Placement of catheter: the catheterization nurse punctures the needle under ultrasound guidance and places the catheter;

d. Cardiac ultrasound-assisted catheter tip localization: ultrasound probe to explore the four-chambered heart section, observe the imaging effect (if the observation effect is not good, observe the short-axis section of the great arteries and subxiphoid section in turn), ultrasound doctor and the placement nurse to cooperate with the placement nurse to send the catheter until the doctor can observe the tip of the catheter under the ultrasound, retain the image to calculate the distance between the tip of the catheter and the septum at the end of cardiac contraction period, L, and the placement nurse to pull out the catheter to the outside. The catheterization nurse pulls the catheter outward for the length of L.

e. Proper fixation of the catheter: The placement nurse continues to complete the subsequent steps to properly fix the catheter.

3. Research intervention program

After patients signed the informed consent form, those who met the inclusion and exclusion criteria were enrolled;

Subjects received TTE-guided catheter placement, and the catheter tip position and procedure time were recorded during placement;

At the end of catheter placement, subjects had CT taken;

The patients were followed up postoperatively for the occurrence of complications (infections);

Analyzing whether there is consistency between TTE-guided catheter tip positioning and CT.

| Personnel Assignment | Assignment |
| --- | --- |

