| One physician | Responsible for the ultrasound localization part of the catheter placement process. |
| One catheterization nurse | Responsible for the catheterization process, cooperating with the doctor to complete the tip positioning. |
| One recorder | A recorder is responsible for recording data on site. |

4. Combination of drugs

This study does not involve the combination of drugs.

5. Research Flowchart

| Trial Flow Chart | | | |
| --- | --- | --- | --- |
| Window period  Trial Procedure | Visit 1  Screening period | Visit 2  Trial period | Visit 3  Observation Period |
|  | -1~0 days | 1 day | 2~ 3 days |
| Signed informed consent | × |  |  |
| Demographic information | × |  |  |
| Medical history and treatment history | × |  |  |
| Determination of inclusion/exclusion criteria | × |  |  |
| Randomization | × |  |  |
| Body temperature | × | × | × |
| Catheter placement |  | × |  |
| Observation and documentation of catheter tip position |  | × |  |
| CT examination |  |  | × |
| Complications | × | × | × |
| Adverse events |  | Continuous observation | |
| Surgical time |  | × |  |
| Nurse Confidence Index |  | × |  |
| Study Summary |  | × | |

6. Study-related laboratory tests

Blood tests (RBC/WBC/PLT/HBG) and coagulation tests (PT/APTT/FIB/D-Dimer/INR) will be completed during the screening period. During the trial and observation periods, if patients develop high fever and are reasonably suspected of having catheter-associated infections, blood cultures are required to confirm the diagnosis of catheter-associated infections.

7. Study-related imaging

Postoperative chest CT should be performed to confirm the location of the catheter tip under imaging.

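### The flow chart schedules the CT that decides the primary endpoint for days 2–3, while the endpoint definition puts it immediately after placement

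*Protocol*

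**What the plan says.** Two statements in the protocol time the CT itself to the placement session:

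- Section VII, evaluation method of the primary endpoint: "chest CT was taken immediately after the subject's operation and interpreted by a physician with relevant experience".
- Section V.3, intervention program: "At the end of catheter placement, subjects had CT taken".

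Two more date the endpoint to the same day without naming the scan:

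- Section VI, observation table: "Precision of catheter tip position | Day of surgery".
- Section VII, heading of the primary endpoint: "Precision of catheter tip position (Time: the day of surgery".

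The flow chart in Section V.5 differs. Its columns for Visits 1, 2 and 3 carry the windows "1~0 days | 1 day | 2~ 3 days" (the first begins at minus 1). Catheter placement and the row "Observation and documentation of catheter tip position" are marked at Visit 2. The row "CT examination" is marked at Visit 3 only, and its Visit 2 cell is empty.

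The synopsis, Section III and Section V.7 say only that the CT follows catheterization or surgery. They fit either timing and do not settle the matter.

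On infection, Section VI has "Postoperative Infection | Postoperative day 3", and Section VII likewise gives three days after surgery.

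**The concern.** The study asks whether a tip placed under TTE guidance is where it should be, with CT as the reference. Under Section VII nothing but the CT classifies a tip as accurate. The TTE reading is taken during placement, so the two methods describe the same tip position only if the CT follows promptly.

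A CT one or two days later describes the tip after an interval in which it may have moved or been adjusted. Section VII itself foresees secondary adjustment: it counts such cases and the time spent on them under Economy, within three days of the intervention. A tip that was correct at placement and moved out would be scored as a TTE failure. A tip that was wrong at placement and was repositioned before the scan would be scored as a TTE success.

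This is not a detail that a statistical analysis plan could repair. It concerns when the image is acquired, and a same-day image that was never taken cannot be recovered in the analysis.

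**Working it through.** **1. Timing, statement by statement**

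| Place in protocol | What it dates | When |
| --- | --- | --- |
| Section V.3 | CT | End of placement |
| Section VII, evaluation method | CT | Immediately after the operation |
| Section VII, endpoint heading | Primary endpoint | Day of surgery |
| Section VI | Primary endpoint | Day of surgery |
| Section V.5, flow chart | Placement and tip reading | Visit 2, day 1 |
| Section V.5, flow chart | CT | Visit 3, days 2–3 |
| Synopsis, Sections III and V.7 | CT | After catheterization or surgery, no window |

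The flow chart separates placement from CT by 2 − 1 = 1 to 3 − 1 = 2 days. The first four rows allow no such gap.

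**2. What one patient is worth**

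The protocol plans 30 subjects and attaches no precision target or power to that number, so there is no sample-size figure to reproduce. One patient is 1/30 = 3.3 percentage points. For scale, 29/30 is 96.7% (exact 95% interval 82.8–99.9%) and 27/30 is 90.0% (73.5–97.9%).

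**3. Illustration of movement out of the zone**

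Let a be the true accuracy at placement and m the share of correctly placed tips that leave the target zone before the CT. Both are assumptions; the protocol gives neither. Expected apparent accuracy is a × (1 − m), and expected patients reclassified are 30 × a × m.

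| a | m | a × (1 − m) | 30 × a × m |
| --- | --- | --- | --- |
| 0.95 | 0.02 | 93.1% | 0.57 |
| 0.95 | 0.05 | 90.25% | 1.43 |
| 0.95 | 0.10 | 85.5% | 2.85 |
| 0.90 | 0.02 | 88.2% | 0.54 |
| 0.90 | 0.05 | 85.5% | 1.35 |
| 0.90 | 0.10 | 81.0% | 2.70 |

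With a CT immediately after placement, m is close to 0 and this component disappears.

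**4. The opposite direction**

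Misplaced tips that are corrected, or move into the zone, before the CT raise the reading. The most this can add is every misplaced tip: 30 × (1 − 0.95) = 1.5 expected patients at a = 0.95, or 30 × (1 − 0.90) = 3 at a = 0.90. The sign of the net bias is therefore not fixed.

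**5. Infection window**

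If flow-chart day 1 is the day of surgery and postoperative days are counted from the day after, Visit 3 covers postoperative days 1–2 and stops short of day 3. If the flow-chart days are read as postoperative days, or surgery day counts as postoperative day 1, the window reaches day 3 at its upper end. The protocol does not say which count applies.

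**The case against.** The best defence is that this is a slip in one table cell. The endpoint definition is explicit, Section V.3 agrees with it, and the study runs at one center with one ultrasound physician, one nurse and one recorder, so staff may simply scan on the day. A cell can also shift when a table is converted from PDF, but the neighbouring rows (placement, tip documentation, surgical time) sit sensibly at Visit 2, which makes that unlikely here. A clerical slip may well be the origin. It remains a written instruction that places the reference scan on a different day from the endpoint it decides.

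Section VI never mentions CT. It dates the endpoint and supports same-day timing only through the definition in Section VII. That is correct, and the contradiction stands without it.

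Four stronger readings are tempting, and the protocol does not support them:

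- *A late CT would measure migration in place of TTE error.* Placement error would still be captured, with later movement added to it.
- *Accuracy would be understated by a known amount.* No migration rate is given, values near zero are possible, and the bias can run in either direction.
- *Some patients will be scanned on the day and others later.* The conflicting instructions permit this, but nothing shows that it would happen.
- *Re-adjustments prompted by a Visit 3 CT would fall outside the three-day economy window.* With placement on day 1, Visit 3 is one to two days after the intervention, so the scan lies inside that window. Nothing indicates that an adjustment would be delayed beyond it.

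On infection, the mismatch depends on the day count. The flow chart also shows continuous adverse-event observation across Visits 2 and 3, and Section V.3 provides for postoperative follow-up of infection. It would go too far to infer that infections are followed for only one day.

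**Conclusion.** The contradiction holds. The flow chart puts the reference CT one to two days after placement, while Sections V.3 and VII put it at the end of, or immediately after, placement, and Sections VI and VII date the endpoint to the day of surgery. Because that CT alone decides the only primary endpoint, this is more than a matter of tidiness: if the flow chart were followed, the accuracy figure would combine TTE placement error with later movement or re-adjustment.

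The size cannot be derived from the protocol. The firm figure is 3.3 points per patient. The range of about 0.6 to 2.9 patients rests on an assumed 95% accuracy at placement, an assumed 2–10% loss and movement in one direction only. The contradiction does not depend on those assumptions.

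The infection-window mismatch is secondary and less certain, since it turns on an unstated day count.

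**What to change.** - Reconcile Sections V.3, V.5, VI and VII to one CT time. Moving the flow-chart CT mark from Visit 3 to Visit 2 brings it into line with the endpoint definition and changes one row. Give Section V.7 the same window.
- State that the primary endpoint is scored on the first CT taken before any re-adjustment of the tip.
- Record the placement-to-CT interval for each patient, so that any late scan is visible.
- State how the flow-chart days relate to postoperative days, and reconcile the Visit 3 window with the infection assessment in Sections VI and VII.

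The CT is already planned, so no extra scan is needed. The cost is a short amendment, one more item on the case form and same-day scanner scheduling.

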The secondary evaluation indexes of this trial are catheterization time, confidence index of catheterization nurses and economy. In the comparison between the two groups, the t-test or Wilcoxon rank-sum test was used to measure the data according to the distribution of , and the chi-square test or Fisher's exact probability method was used to count the data.

6. Safety evaluation index

Safety evaluation was based on the safety analysis set (SS).

7. Adverse events

Adverse events, serious adverse events, device-related adverse events (or serious adverse events) that occurred during the study were described in terms of number of cases, number of cases, and incidence rate, and the specific manifestations, frequency, severity, and relevance to the device were described for all adverse events. Describe the type, number of cases, and incidence of device defects.

8. Vital signs

Statistical descriptions of changes in vital signs from baseline to post-treatment time points were performed for each group separately, including the number of subjects, mean, standard deviation, median, minimum, and maximum values. Measurement data were analyzed by group t-test or Wilcoxon rank-sum test, and count data were analyzed by two independent samples chi-square test or Fisher's exact probability method.

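### The two operator-confidence questions lead towards a favourable answer and name neither TTE nor a comparator, and question 3 falls outside the outcome's own definition

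*Protocol*

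**What the plan says.** Section VII of the Protocol lists confidence of the catheterization operator among the secondary indicators and defines it as "Confidence of the catheter placement operator in positioning the catheter tip to the optimal position with ultrasound assistance". The method is described as follows: "A qualitative interview was conducted in the form of a postoperative interview with the catheterization operator". A five-question outline follows. Question 1 asks about experience and question 2 about past difficulty in positioning the tip. The two questions on confidence are:

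- Question 3: "Do you feel more confident in your operating technique when ultrasound-assisted catheterization is performed"
- Question 4: "Do you feel more confident in positioning the catheter in the optimal position when ultrasound-assisted catheterization is performed"

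Question 5 asks whether the operator would "think that the use of ultrasound interferes with your catheterization".

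Section V (Methods) uses ultrasound at two points of the same procedure. In step c, "the catheterization nurse punctures the needle under ultrasound guidance and places the catheter". Step d is headed "Cardiac ultrasound-assisted catheter tip localization" and is carried out by the ultrasound doctor with the nurse cooperating.

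The answers are to be used as an endpoint. The flow chart in section V schedules a nurse confidence index, and section XI states: "The secondary evaluation indexes of this trial are catheterization time, confidence index of catheterization nurses and economy".

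**The concern.** A confidence outcome can support the technique under study only if its questions ask about that technique and leave room for any answer. Here the procedure contains two ultrasound steps, and only the second, TTE localization of the tip, is being studied. The questions use a general phrase about ultrasound assistance that can be read to cover both. They also ask only about an increase in confidence and do not state what it is compared with.

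At stake is the meaning of the confidence result. A report that the nurse felt more confident could be presented as evidence for TTE localization although part of it reflects the puncture, or agreement with a leading question. The wording is written into the Protocol itself, so it is not a detail left to a later analysis plan.

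**Working it through.** No arithmetic applies. The Protocol gives no figure for this outcome, and the point turns on wording. The check sets the questions beside the outcome definition and the procedure steps.

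| Item | Subject of the question | Direction offered | Comparator named | TTE named | Within the definition |
|---|---|---|---|---|---|
| Definition (VII) | placing the tip optimally | none | no | no | – |
| Question 3 | operating technique in general | more | no | no | no |
| Question 4 | placing the catheter optimally | more | no | no | yes |
| Question 5 | interference from ultrasound | unfavourable | no | no | no (a different matter) |

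**Direction.** Both of the two confidence questions ask only about an increase. A no is possible, but it would not separate unchanged confidence from reduced confidence. Question 5 invites an unfavourable view, but about interference. An operator may find the probe in the way and still be more confident about the tip, so question 5 offsets the lean only in part.

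**Comparator.** To feel more confident requires a reference. Neither question gives one, although the Protocol has a candidate: section VIII calls ECG-guided tip positioning the conventional method. Without a named reference, the operator may be comparing with ECG guidance, with placement without any ultrasound, or with her or his own earlier practice.

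**Which ultrasound, question 3.** The respondent is the catheterization nurse. Under section V the nurse performs the ultrasound-guided puncture in step c, while the doctor performs the cardiac scan in step d. Asked about her or his own technique when ultrasound assists, the nurse could reasonably have step c in mind. A yes to question 3 therefore cannot be assigned to TTE with assurance. Whichever step is meant, technique in general is wider than the outcome defined in the same section.

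**Which ultrasound, question 4.** The subject is reaching the optimal position. Step d addresses the position of the tip; the puncture in step c does not. The heading of step d also describes TTE as assisting, whereas step c speaks of guidance. In context, question 4 points to TTE. The defect here is a loose phrase, a one-way stem and a missing comparator.

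**Use of the answers.** Section VII calls the interview qualitative, while sections V and XI call its result an index. If the answers are condensed into an index, the wording of the questions determines what that index measures. Section V assigns all placements to one nurse, so there are no other respondents whose different reading would reveal the ambiguity.

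**The case against.** Several points on the other side are sound.

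- **The Protocol's vocabulary favours TTE.** Assistance is the word used for step d and not for the puncture, and section IX says that a doctor carried out all applications of ultrasound in the trial. This stands for question 4. It does not rescue question 3, which is about technique in general and is put to the person who does the puncture.
- **It is an interview outline, not a closed questionnaire.** An interviewer can probe and clarify, and there are no fixed response options. This stands in part: nothing in the outline requires such probing, and the result is elsewhere called an index.
- **The text is visibly a translation.** Chinese remains in formulas, and question 5 has lost its subject. The interview actually used may be worded better, and its source-language text is not at hand. This is a fair reason for modest confidence in the point.
- **Little hangs on it.** The synopsis does not list confidence among the secondary outcomes, one nurse answers, and rewording does not make one person's view generalizable. This stands, and it sets the rank of the point.

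A reader might go further and infer that the questions presuppose the favourable answer, or that no yes can be attributed to TTE and the outcome says nothing about tip localization. The Protocol does not support that. A no can be given, question 5 asks for an unfavourable view, and question 4 follows the definition and addresses what step d does.

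**Conclusion.** The point holds as a minor one. Both confidence questions lead in one direction and name neither a comparator nor TTE. Question 3 lies outside the outcome's definition, and a yes to it could reflect the ultrasound-guided puncture. Question 4 measures the defined outcome, with its attribution to TTE loosely worded but not lost.

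The size of any resulting bias cannot be estimated from the document. Its reach is limited to one secondary outcome answered by one nurse. The primary outcome, tip position read on postoperative CT, is unaffected, as are the safety outcomes.

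The conclusion assumes that the English wording reflects the questions as put to the nurse, and that the answers will be used as the secondary index that section XI lists.

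**What to change.** Revise the interview outline in section VII:

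- Drop question 3, or restrict it to positioning the tip.
- Reword question 4 neutrally and name both methods. For example: *Compared with your usual method of locating the tip (such as the ECG-guided method that the protocol calls conventional), is your confidence that the tip is in the target position lower, the same or higher when TTE is used to locate it?* The ECG method is given only as an example because the Protocol does not say what this nurse's own usual method is.
- Name TTE in question 5, so that it is clear which ultrasound might interfere.
- Follow each question with an open prompt asking for reasons, so that the interview stays qualitative.

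The cost is a change to the outline. It needs no additional patients, staff, visits or measurements. Interviews already held with the present wording should be reported with that wording and kept apart from later ones.
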